### Health economic study

We will perform a cost-consequence analysis of the iHOST intervention compared to not using it, in terms of cost per OST prescription, cost per patient-directed discharge prevented and cost per 28-day emergency readmission prevented. Analysis will use an NHS cost perspective and include each of the main elements of the intervention (MyMedsCard, helpline, OST champion and the e-learning module) as well as the costs of OST prescription within the hospital setting. As the opioid withdrawal management policy guideline will not need to be developed again on roll-out of the intervention, we assume this cost to be negligible and will therefore not conduct a detailed cost estimate of the policy development. We will include the cost savings for 28-day emergency visits prevented, but will exclude the costs of unrelated hospital visits.

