### Safety

iHOST may involve changes to OST prescribing in participating hospitals. Changes to guidelines and clinical processes will be agreed through existing clinical governance structures at participating hospitals and will become part of usual care. Potential safety issues will be identified through these processes. Where events occur that may be related to the safety of new OST pathways, the events will be reviewed by the participating hospital. If the participating hospital assesses that the event was at least partly attributable to the new protocol, all partner hospitals together with the iHOST team will together review whether changes across all iHOST sites are necessary.

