We will evaluate the intervention using a pragmatic mixed-methods approach. This will provide a holistic understanding of the intervention’s costs and benefits. We chose this approach over a cluster randomised trial for three reasons. First, such a trial would be expensive. Second, the barriers to implementation are different in each hospital and iHOST is focused on developing an intervention that is suitable for each site, rather than a consistent intervention. Third, we do not necessarily expect a clear effect on a single primary outcome. Given the marginalisation of the patient group and the long histories of adversity that many have experienced, it is possible that many patient-directed discharges will occur despite better OST and better patient care. Our engagement with patients and staff suggests that better OST could reduce suffering and increase trust between staff and patients even if primary outcomes in our quantitative study do not appear to change significantly. We wanted to capture these holistic outcomes.

Key limitations are:

1. 

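### The economic analysis credits readmissions avoided but lists no cost for the longer index stay that an avoided patient-directed discharge would be expected to bring

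*Protocol article*

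**What the plan says.** The Health economic study section plans a cost-consequence analysis with three results: "cost per OST prescription, cost per patient-directed discharge prevented and cost per 28-day emergency readmission prevented". On scope it says: "Analysis will use an NHS cost perspective and include each of the main elements of the intervention". The items named are "MyMedsCard, helpline, OST champion and the e-learning module) as well as the costs of OST prescription within the hospital setting". Development of the clinical guideline is set aside as negligible. The offset and the one further exclusion come in a single sentence: "We will include the cost savings for 28-day emergency visits prevented, but will exclude the costs of unrelated hospital visits".

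Three other places bear on this:

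- The Introduction describes patient-directed discharge as patients going before their treatment is complete.
- The Discussion says that such discharge is associated with readmission, and that better OST is expected to reduce both.
- The economic limitations in the Discussion cover uncertainty about prescribing, generalisability and the absence of long-term modelling. The only sensitivity analysis named varies prescribing rates without iHOST. Index stay does not appear.

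**The concern.** The intervention is meant to keep patients in hospital who would otherwise have left early. If it works, the most direct resource consequence is more bed-days in the index admission, paid by the same NHS budget that gains when a readmission is avoided. The stated scope takes the later saving and does not list the earlier cost that is expected to go with it.

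This matters most for the cost per patient-directed discharge prevented, because the added stay is part of what preventing that event involves. It carries over to the cost per readmission prevented if the same net cost is the numerator. Both figures would inform hospitals deciding whether to adopt iHOST, and a hospital would meet the extra bed-days whether or not the analysis had counted them.

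**Working it through.** The economic section gives no unit cost, length of stay or net cost, so there is no planned figure to reproduce. What follows is an illustration of scale.

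**Inputs from the protocol**

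- Table 1, calendar year 2021, iHOST sites: A 349, B 662, C 624. The table labels these as patients, while the Population paragraph defines the unit as emergency admissions; I treat them as admissions.
- Table 1 percentages recomputed from their counts agree. Patient-directed discharge: 70/349 = 20.1%, 149/662 = 22.5%, 116/624 = 18.6%. Readmission: 101/349 = 28.9%, 214/662 = 32.3%, 148/624 = 23.7%.
- Effect assumed in the Power paragraph: 5 percentage points on each outcome.

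**Inputs assumed here, not in the protocol**

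- e = extra index bed-days per patient-directed discharge averted, 1 to 6.
- L = bed-days per readmission averted, 2 to 8.
- c = cost of a bed-day, taken as equal in the index stay and the readmission.

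**Step 1: events averted per year.** 349 + 662 + 624 = 1,635, and 0.05 × 1,635 = 81.75, about 82 of each outcome (A 17.45, B 33.10, C 31.20).

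**Step 2: share of the credited saving that is offset.**

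- Credited saving = 81.75 × L × c
- Unlisted cost = 81.75 × e × c
- Share offset = e/L

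| | e = 1 | e = 2 | e = 4 | e = 6 |
|---|---|---|---|---|
| L = 2 | 50% | 100% | 200% | 300% |
| L = 4 | 25% | 50% | 100% | 150% |
| L = 6 | 17% | 33% | 67% | 100% |
| L = 8 | 12.5% | 25% | 50% | 75% |

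In bed-days at L = 4, the saving as planned is 81.75 × 4 = 327. Net of index stay it is 81.75 × (4 − e): about 245 at e = 1, 164 at e = 2, 0 at e = 4 and −164 at e = 6.

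**Step 3: effect on the ratio.** Adding the unlisted cost raises the cost per patient-directed discharge prevented by (81.75 × e × c) / 81.75 = e × c. The number of events cancels, so this ratio is understated by e bed-day costs whatever the size of the effect. The cost per readmission prevented moves by the same amount only if equal numbers of the two events are averted.

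**The case against.** The strongest reply is that index stay is unmentioned, not excluded. The section is one paragraph of a journal article, and resource items and unit costs are commonly left to a fuller plan. This stands to the extent that nobody can say the team has decided against counting index stay. It does not dispose of the point, because the paragraph goes beyond a general statement: it names the costs, the saving and the exclusions. Someone following it as written would leave index stay out.

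A second reply is that the direction of the error is not proven. The protocol gives no length-of-stay data. It also allows that iHOST may bring patients in earlier, which could alter case mix and shorten stays. This stands too. A longer stay is what the described mechanism leads one to expect, not a result. The 5-point effect is a power input, and e and L are my assumptions.

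Three stronger readings are tempting and are not supported:

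- **The guideline cost.** A reader might set "guideline will not need to be developed again on roll-out of the intervention, we assume this cost to be negligible" against "iHOST is focused on developing an intervention that is suitable for each site, rather than a consistent intervention" and "Changes to guidelines and clinical processes will be agreed through existing clinical governance structures at participating hospitals", and infer that a guideline rewritten for every hospital is being costed at nothing. The intervention section describes one guideline, the tailoring remark concerns the intervention as a whole, and agreement through local governance is approval, not redevelopment. The text says negligible and gives its reason.
- **The unrelated-visits exclusion.** A reader might infer that it clashes with an all-cause readmission outcome. The article never uses that term and places its variable definitions in Extended Data, which is not shown.
- **The sign of the result.** A reader might infer that iHOST would raise net NHS cost. The table includes such cells, but they come from the assumed e and L.

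**Conclusion.** The point holds as a one-sided cost scope. The listed items credit avoided readmissions and leave out the index bed-days that avoided patient-directed discharges would be expected to add, and the stated limitations and sensitivity analysis do not cover the gap. The tendency is to make the cost per patient-directed discharge prevented and the cost per readmission prevented look too favourable.

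The magnitude is undetermined. An offset of about 12% to 300% of the readmission saving reflects assumed lengths of stay, equal bed-day costs, equal numbers of each event averted and the 5-point effect. If iHOST produced no net increase in index stay, there would be no bias. That is a reason to measure index stay rather than leave it off the list. The point concerns a secondary analysis and does not touch the two primary clinical outcomes.

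**What to change.** In the Health economic study section, add the bed-day cost of the index admission to the listed costs. Estimate it by applying the planned difference-in-difference model to index length of stay, derived from the admission and discharge dates in Hospital Episode Statistics. Study entry should be at admission, as already planned for patient-directed discharge. Take the estimate over all eligible admissions, since individual averted discharges cannot be identified. The mean difference multiplied by the number of admissions gives the net change in bed-days, including any shortening from earlier presentation. Value those days on the same basis as the readmission days, and report the cost ratios net of them, with their uncertainty. If the team already means to count index stay, one sentence saying so and naming the method is enough.

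The price is one more model on admissions already being extracted, plus a bed-day cost, which the article does not give. The result may be less favourable to iHOST, and it will be noisier because the variability of length of stay enters the net cost.

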### Safety

iHOST may involve changes to OST prescribing in participating hospitals. Changes to guidelines and clinical processes will be agreed through existing clinical governance structures at participating hospitals and will become part of usual care. Potential safety issues will be identified through these processes. Where events occur that may be related to the safety of new OST pathways, the events will be reviewed by the participating hospital. If the participating hospital assesses that the event was at least partly attributable to the new protocol, all partner hospitals together with the iHOST team will together review whether changes across all iHOST sites are necessary.

### Ethics and approvals

Ethical approvals have been received from the NHS Health Research Authority on 8 September 2022 [Ref 133022], the Camden and Islington NHS Research Ethics Committee on 31 May 2022 [Ref 22/LO/0370] and the LSHTM Observational Research Ethics Committee on 18 July 2022 [Ref 27895]. Local research and development approvals have been obtained from each hospital site and participating drug treatment service.

The difference-in-difference study was approved by the UK Health Security Agency Research Ethics and Governance Group on 29 March 2022 [R&D ref 497].

## Discussion

Poor OST in acute hospitals is a barrier to effective care for patients who use illicit opioids. This is clear from our research in the UK
^
33–
35
^, engagement with affected groups, and international evidence
^
8,
13,
14,
23,
36,
37
^. Poor OST can cause physical and psychological distress and result in treatment interruption or patients leaving hospital to obtain illicit drugs
^
8,
13
^. People experiencing opioid withdrawal can be perceived as challenging by healthcare workers. Improving care for patients who use illicit opioids and their feeling of safety could be beneficial for both patients and hospital staff. Although there are well-documented problems with OST in hospitals
^
6–
10
^, this has not led to evaluated interventions in the UK.

Barriers to better OST have been investigated, and qualitative evidence has found procedural and attitudinal barriers. For example, medical professionals often have negative attitudes towards patients who use opioids, which may impact care
^
10,
38
^. Fear and experience of drug withdrawal are key risk factors for patient-directed discharge
^
13,
39
^, which is associated with hospital readmission and increased mortality risk
^
40–
44
^.

iHOST is designed to address these barriers using a multi-component intervention that addresses procedures, knowledge, and attitudes. It is an applied research project in which the intervention is developed in a real-world setting. If successful, it should improve management of withdrawal and reduce delays in the prescription of OST. We anticipate that improvement of OST will lead to improved patient care, improved patient experiences, a reduction in patient-directed discharge, and reduced re-admissions.

We will evaluate the intervention using a pragmatic mixed-methods approach. This will provide a holistic understanding of the intervention’s costs and benefits. We chose this approach over a cluster randomised trial for three reasons. First, such a trial would be expensive. Second, the barriers to implementation are different in each hospital and iHOST is focused on developing an intervention that is suitable for each site, rather than a consistent intervention. Third, we do not necessarily expect a clear effect on a single primary outcome. Given the marginalisation of the patient group and the long histories of adversity that many have experienced, it is possible that many patient-directed discharges will occur despite better OST and better patient care. Our engagement with patients and staff suggests that better OST could reduce suffering and increase trust between staff and patients even if primary outcomes in our quantitative study do not appear to change significantly. We wanted to capture these holistic outcomes.

Key limitations are:

1. 
**Process evaluation.** (a) The research team involved in intervention development will also oversee the process evaluation. This might inhibit some staff and stakeholders from expressing robust critique of the intervention, particularly if interviewed by researchers recognisable from e-learning training videos. A different team member will, therefore, conduct most of the qualitative interviews after the intervention has launched at the evaluation sites. (b) We will recruit inpatients who use opioids through hospital staff. This is crucial to ensure patients are well enough to consent, are present on the ward, and meet inclusion criteria (ie, use opioids). This can however, facilitate ‘gatekeeping’, whereby patients likely to provide a favourable impression of the hospital or intervention are selected for interview. In building relationships with hospital staff, we will stress the need to talk with a diversity of patients and the learning to be gained from understanding less positive experiences. (c) Observations include active shadowing of hospital staff on ward rounds. The presence of the researcher, and their association with the intervention, can impact staff-patient dynamics observed. Detailed field notes will be taken for all site visits, including interviews and staff training sessions, to provide additional context. (d) The three hospitals participating in iHOST may be more motivated or otherwise optimised for successful implementation. Recommendations for roll-out will need to account for potential additional barriers such as the absence of a motivated senior ‘champion’.2. 
**Controlled difference-in-difference study.** (a) No data will be available on OST prescriptions, either in the community or in hospital. Ideally, our study would include patients who had a community OST prescription prior to admission. Instead, we will use patients with a diagnosis of ‘opioid dependence’ as a group that may benefit from iHOST. This may dilute the effect of iHOST because some participants will not have prescriptions of OST; (b) the study will not capture any effect on patients’ propensity to seek treatment. Part of the rationale for iHOST is that people who are dependent on opioids avoid or delay hospital treatment because they anticipate poor OST. This study investigates outcomes after admission and will not capture any effect on patients’ propensity to seek treatment in hospital. If iHOST leads to more patients seeking hospital care or presenting earlier, this may cause residual confounding because patients after implementation will differ from those before; (c) The study will only estimate effects on patient-directed discharges and readmissions. These outcomes are based on previous research, patient and public involvement, and the availability of data in HES. Other important outcomes may be affected by iHOST, such as the quality of medical treatment, patient satisfaction, continuation of OST in the community, and use of illicit drugs. Other parts of the evaluation seek to understand broader outcomes. A more detailed list of limitations for the difference-in-difference study is provided in Extended Data
^
32
^.3. 
**OST process measures**. These measures are intended to support iHOST sites to learn about the quality of OST in their setting and identify opportunities for ongoing improvement. They are not a robust approach to estimating the impact of the intervention, as a change in these measures could be attributed to many factors other than the intervention, such as changing patient demographics, changing use of OST (eg. if iHOST leads to different types of patients being given OST), and wider healthcare policies.4. 
**Health economic study.** We may not be able to accurately estimate the difference in methadone prescriptions. In many cases methadone may have been prescribed without the iHOST protocol, but having the protocol in place may mean that it is prescribed more quickly. We will do sensitivity analysis around this, assuming ranges in counterfactual prescription rates without the iHOST protocol in place. Costs included in the economic evaluation will be specific to sites where the study is operating and may not be generalisable to other settings or implementation of iHOST at large scale. We are unable to do any modelling of long-term outcomes, and therefore cost and effect estimates may not include important future events.

## Conclusions

This work aims to recognise that patients who use illicit opioids are often vulnerable and require support in their journey through the healthcare system. iHOST aims to promote a culture change in which patients who use opioids feel confident to access medical care. This can also benefit providers and staff who sometimes feel unconfident working with this group and may consider them ‘challenging’. iHOST training will provide skills in de-escalation strategies and culturally safe communication. The work with clinical policies will address procedural barriers to OST provision. We hope these changes will improve medical care and reduce health inequality.

## Data Availability

No data are associated with this article. LSHTM Research Online: Extended data for ‘Improving hospital-based opioid substitution therapy (iHOST): protocol for a mixed-methods evaluation’,
https://doi.org/10.17037/PUBS.04671913
^
32
^ This project contains the following extended data: Definitions of variables for difference-in-difference study Limitations for difference-in-difference study Data are available under the terms of the
Creative Commons Attribution 4.0 International license (CC-BY 4.0)
